### Data collection and analysis

#### Cervical screening data.

The primary outcome will be the number and proportion of Aboriginal and Torres Strait Islander women and people with a cervix who are overdue for cervical screening (under-screened) or have no recorded history of a cervical screen (never-screened) at the completion of the study, compared to the before period. Secondary outcomes are cervical screening participation, the number and proportion of cervical screens conducted by collection type (self-collect versus clinician collect) and HPV positive tests in the 2-years before and during the study period. Quantitative outcomes data will be obtained using one or a combination of the following pathways to be determined by the services’ preferences: from local practice management software, practice audit tools, from the National Cervical Screening Register (NCSR) and/or manual audit of relevant patient records. De-identified data will be provided to nominated members of the research team via secure methods.

### Analysis

Primary and secondary outcomes will be calculated comparing data from the before (*T0*) and after (*T1*) period. Retention of effects will be measured for services who provide data at 3- and 6-month intervals in the post-implementation period. For the primary outcome, the number and proportion of all screen eligible clients at the services who are under-screened or never-screened at *T1* compared to *T0* (number of under- and never-screened screen eligible clients/number of screen eligible women). Secondary outcomes are cervical screening participation rate (number with a recorded cervical screen in the previous 5-years/number of screen eligible clients), and the number and rate of cervical screens conducted using self-collection (number of tests conducted using self-collection/number of screening tests), and the HPV positivity (number of HPV positive tests/number of screening tests). Descriptive analysis will be used to analyse cervical screening data, with regular interim reports made available to participating services. Primary and secondary outcomes will be calculated comparing data from the before (T0, > 24 months) and after (T1, 12 months) period. The before and after intervention periods will be compared descriptively, and using multi-level logistic regression models clustered on site and allowing for participants who are active in both periods. Due to the small number of participating services, modelled findings and secondary subgroup analyses will be interpreted cautiously, with emphasis on direction and magnitude. A subgroup analysis will also be conducted of the primary outcome among women who have never screened or screened >10 years ago. These will be considered exploratory with no adjustment for multiplicity planned given the implementation focus. Data will be analysed using Microsoft Excel (Microsoft Corporation) and STATA software (StataCorp, version 18).

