### Rationale and aims

Applying Rigney’s Indigenist Research approach to implementation [29] and guided by the Lowitja Institute Evaluation Framework [30], this study aims to increase cervical screening participation among under- and never-screened Aboriginal and Torres Strait Islander women and people with a cervix in partnership with ACCHOs by implementing HPV self-collection into practice.

The objectives of *Screen Your Way* are to:

1.Co-design, implement and evaluate models to support HPV self-collection and other strategies that increase cervical screening within ACCHOs2.Assess the impact of HPV self-collection implementation models on cervical screening participation3.Explore providers’ and clients’ views and experiences of the project to provide context for the cervical screening participation data and inform the evaluation of the implementation strategies4.Disseminate findings to assist with the evidence based national scale up of HPV self-collection.

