### Sample size

As per clinical guidelines, any women and people with a cervix who have not screened under the new HPV screening program will be considered under screened (at least four years overdue); this equates to about 50% or more of eligible screen eligible clients at the services. The baseline screening rate assumption is that 5–10% of screen eligible women and people with a cervix currently move from under screened to screened per 12 months; assuming an increase with policy change to open access to self-collection in 2022 (prior to study intervention) to 20% per 12-month period. To detect a doubling in participation among under screened women and people with a cervix, from 20% in 12 months at baseline to 40%, with 80% power (2-alpha = 5%) and a conventional non-clustered design, would require 91 women and people with a cervix per arm. Allowing up to 12 clusters before and after, and assuming a conservative Intraclass correlation coefficient (ICC) of 0.1, then an average of 50 women and people with a cervix per cluster per period would give a design effect of 5.9, so a total of 1074 women and people with a cervix are required, rounding up to 1200 women and people with a cervix (600 before period, 600 after period). This is feasible given the typical service populations of ACCHOs and the chosen jurisdictions.

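### The primary outcome nets clients brought into screening against clients who fall newly overdue, and no listed outcome measures the uptake among under-screened clients that the aim and sample size concern

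*Protocol article*

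**What the plan says.** All references are to the protocol article.

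- **Primary outcome.** The Cervical screening data section counts clients "who are overdue for cervical screening (under-screened) or have no recorded history of a cervical screen (never-screened) at the completion of the study", compared with the before period. The Analysis section takes "the number and proportion of all screen eligible clients at the services who are under-screened or never-screened" and gives the ratio as "number of under- and never-screened screen eligible clients/number of screen eligible women", at T1 against T0.
- **Secondary outcomes (Analysis).** The first is 5-year participation, "number with a recorded cervical screen in the previous 5-years/number of screen eligible clients". The others are the self-collected share and HPV positivity, both with screening tests as denominator.
- **Aim (Rationale and aims).** "this study aims to increase cervical screening participation among under- and never-screened Aboriginal and Torres Strait Islander women and people with a cervix".
- **Sample size.** The effect to detect is a rise from 20% to 40% in 12 months among under-screened clients. Here under-screened means not yet screened under the HPV programme, and "this equates to about 50% or more of eligible screen eligible clients at the services".
- **Analysis model.** A multi-level logistic regression clustered on site, allowing for participants active in both periods. An exploratory subgroup covers clients never screened or last screened more than 10 years ago.
- **Evaluation Framework.** Success is judged partly against 70% participation.

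**The concern.** The primary outcome is a status read at two dates over the whole eligible list. Between those dates two things happen: under- and never-screened clients are screened, and clients who were up to date become overdue. The change in the proportion is the difference between the two. Only the first movement answers the aim, and only the first was used to size the study.

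The listed secondary outcomes do not separate them. Under the overdue rule, 5-year participation is close to 100% minus the primary outcome, and the other two say nothing about who was under-screened beforehand. A service could reach many under-screened clients and show a modest net change because many routine clients lapsed. Another could show a similar change mainly by re-screening its regulars on time. The Analysis section relies on direction and magnitude, and magnitude is what netting affects.

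**Working it through.** **Step 1: the plan's own figure.** For 20% versus 40% with 80% power and two-sided 5%, a two-proportion calculation gives 91 per arm with continuity correction (82 without). The design effect is 1 + (50 − 1) × 0.1 = 5.9. The total is 2 × 91 × 5.9 = 1073.8, that is 1074. The stated numbers reproduce, so the powered contrast is conversion among the under-screened. With 600 per period the effective size is 600 / 5.9 = 101.7, which gives about 88% power for that contrast (without continuity correction).

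**Step 2: what the primary outcome measures.** Take a fixed client list over 12 months, with

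- U = share under- or never-screened at T0, and S = 1 − U;
- c = share of those clients screened during the year;
- d = share of up-to-date clients who fall due in the year;
- r = share of those due who are re-screened.

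Change in the primary proportion = −c × U + d × S × (1 − r).

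Inputs: U is 50% (Sample size: about 50% or more) or 58% (Introduction: 42% screened within five years). c is 20% or 40% (Sample size). d is not in the documents; one fifth is assumed from the 5-year look-back with screens spread evenly. r is not given, so it runs from 0 to 100%.

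**Step 3: results in percentage points, d = 1/5.**

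| U | Clients due (d × S) | c = 40%: r = 100% to r = 0 | c = 20%: r = 100% to r = 0 |
|---|---|---|---|
| 50% | 10.0 | −20 to −10 | −10 to 0 |
| 58% | 8.4 | −23.2 to −14.8 | −11.6 to −3.2 |

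For example, at U = 50%, c = 40%, r = 0: −0.4 × 0.5 + 0.2 × 0.5 = −0.10.

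**Step 4: when do 40% and 20% uptake give the same score?** This requires 0.2 × U = 0.2 × S × (difference in r), so the difference in r must equal U / S. At 50% that is 1: one service re-screens none of its due clients and the other all of them. At 58% it is 0.58 / 0.42 = 1.38, which is impossible; the nearest approach is −14.8 against −11.6. Smaller differences in uptake are easier to mask. At U = 50%, 40% uptake with 25% of due clients re-screened gives −20 + 7.5 = −12.5, and 30% uptake with 75% re-screened gives −15 + 2.5 = −12.5.

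**Step 5: sensitivity to d.** With d = 1/10 and U = 50%, 5 points fall due. Then 40% uptake gives −20 to −15 and 20% uptake gives −10 to −5, and the ranges no longer meet.

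**Step 6: which definition applies.** Implementation runs from September 2024 to September 2026 (Setting). With a 5-year look-back, the screens ageing out date from about September 2019 to September 2021, after the December 2017 change to HPV testing. Under the overdue rule those clients re-enter the numerator. Under the Sample size rule they do not, because they have been screened under the HPV programme. The second term is then near zero and the change is about −c × U: −20 against −10 points at U = 50%.

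**The case against.** A reader might infer that a service doubling uptake and one that merely re-screens its regulars would score identically. The documents do not support that as a general statement. They put the under-screened at about 50% or more, and the Introduction's figure implies 58%. With one fifth due, a tie between 40% and 20% uptake is possible only at 50% or below, and at 50% it needs re-screening of 0% against 100%. The example strategies include reminders to clients who are due and status checks at routine visits, so no re-screening at all is unlikely. At equal re-screening, the service with 40% uptake is ahead by 0.2 × U, or 10 points at 50%. All of this stands.

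The even spread of due dates is also open to challenge. The sample-size text assumes uptake rose after the 2022 policy change, so the oldest fifth of the look-back may hold fewer than one fifth of the screens. Ten points due is then too high. This stands as well, and Step 5 shows that it matters.

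The net proportion has a purpose. The Evaluation Framework uses a 70% participation target, and Objective 2 concerns participation in general. A reader might conclude that the net proportion is the wrong measure, or that 5-year participation is redundant and can go. Neither follows: both describe coverage and should stay. What they cannot do is show by themselves that under-screened clients were reached.

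The exploratory subgroup is a partial safeguard, since a client falling due at five years cannot enter the more-than-10-years group within 12 months. It omits clients overdue by less. Allowing for participants active in both periods handles correlation but does not turn the outcome into conversion.

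Finally, a finer split could sit in an analysis plan that is not shown. The mismatch between the stated primary outcome, the stated aim and the powered effect is in the article itself.

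**Conclusion.** The point holds in limited form. Under the overdue rule the primary outcome is a net of two movements, the aim and the sample size concern one of them, and no listed primary or secondary outcome measures that one. With 50% under-screened and an assumed one fifth of up-to-date clients due per year, the full planned effect can appear as anything from a 10- to a 20-point fall, and no change in uptake as anything from 0 to 10. At 58% the ranges are 14.8 to 23.2 and 3.2 to 11.6 and do not overlap. So the signal is blurred, not erased.

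The size rests on a fixed client list, an assumed due rate and unknown re-screening. It also depends on the definition of under-screened: if the Sample size rule governs the numerator, the netting largely vanishes. That the two sections differ is itself something to settle.

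**What to change.** 1. Reconcile the Cervical screening data and Analysis sections with the Sample size section, and use one definition of under-screened throughout.
2. Keep the net proportion and 5-year participation. Add, as a named key outcome, 12-month conversion: among clients under- or never-screened at the start of a period, the share screened in the next 12 months. Compute it the same way for a 12-month before period and for the implementation year, and compare the two with the planned site-clustered model. The before period must also be 12 months, because the Analysis section now sets a before period of more than 24 months against 12 months after. A T0-by-T1 table alone would give conversion for the implementation year only, with no comparator. This is the contrast that the sample size powers.
3. Report separately the clients who fell due in each period, by whether they were re-screened.
4. Base statements about reaching under- and never-screened clients on the conversion comparison.

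Cost: wording and a modest extra tabulation and model. The planned model for participants active in both periods already implies linked client-level data. The downsides are that conversion covers only clients present at the start and end of a period, and that the before period needs the earlier screen date, so services able to supply only aggregate data may not contribute.

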### Step 2: Co-design of strategies for implementing self-collection at each site

We will work with nominated staff at participating services to facilitate co-design workshops, set priorities collaboratively, and design locally tailored strategies, engaging community members as determined by each service. This process will follow key principles of co-design with Aboriginal and Torres Strait Islander peoples, including leadership, cultural grounding, respect, benefit to community, inclusive partnerships, transparency, evaluation, and reciprocity [40,41].

Co-design will occur through a structured yet flexible and iterative process facilitated by the research team and tailored to each site. We will begin by meeting with nominated service staff, often those involved in cervical screening or research, to agree on the preferred approach and identify who should participate, such as other clinical staff, non-clinical staff, and local community members or groups. Each site will be offered up to two in-person visits; however, workforce availability and geographic challenges may mean many engagements occur online, supplemented by virtual planning meetings and collaborative workshops.

While co-design will be guided by each service, it will broadly address local priorities and goals for cervical screening, explore context, identify barriers and facilitators, and develop strategies to enhance access. These ideas will be refined into implementation strategies through multiple interactions between the research team and service staff. This iterative approach allows strategies to evolve in response to feedback and context, ensuring each solution is tailored to the unique needs of the service. In practice, this means strategies may iteratively develop over the course of the implementation period as new priorities are identified. There will be no predetermined list of strategies; all ideas will emerge through co-design to support local needs. However, a common focus across sites will be improving data support and access. Strategies to achieve this will vary depending on local systems and capacity. All strategies will aim to increase participation of under- and never-screened women and people with a cervix in cervical screening using HPV self-collection. Strategies may include community engagement, participant-level interventions, workforce development, and system or service-level changes.

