
### Step 4: Evaluation

#### Evaluation Framework.

The evaluation of this research will be conducted within an overarching conceptual framework that combines key constructs from the RE-AIM Framework [43] with the Health Equity Implementation Framework [44]. The evaluation variables are outlined in Table 1. During the co-design process services may identify additional variables or research questions of interest to their unique context and these will be added to the evaluation framework. Quantitative data will be used to assess intervention impact, interpreted alongside an understanding of how colonial health structures shape outcomes. Indigenist qualitative methods will provide context, centring participants’ experiences, voices, and definitions of meaningful change. Evidence of “success” will be judged equally by increases in the primary outcome toward cervical screening elimination targets (i.e., 70% participation) and by the extent to which participants define the co-design and implementation phases as “successful”, including the degree to which these practices embody sovereignty and support health system (re)build.

**Table 1 pone.0336004.t001:** Evaluation variables.

Approach	Collection methods	Variables
Quantitative	• De-identified data extracted from service Record Management Software and/or Clinical Audit Tools at baseline (#T0), periodic intervals as determined by each service (approximately 3 monthly), and 12 months for pre-post analysis (#T1). Services can provide data at 3 and 6 months post implementation.	De-identified cervical screening data for screen eligible Aboriginal and Torres Strait Islander clients at each service (number and proportion): • Cervical screening participation #T0, #T1 • Under-or never-screened #T0, #T1 • Cervical screens by collection method (i.e., self- or clinician-collection) #T1 • HPV positive tests #T1
Qualitative	• Qualitative Yarns and Yarning circles with ACCHO staff and eligible clients (women and people with a cervix)	• Yarns will cover topics such as: experience of participating in or implementing strategies; perceptions of effectiveness; reach and sustainability of strategies; challenges and strengths throughout implementation period.

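### HPV positivity is compared before and after over all tests combined, so the change also reflects the planned shift towards under-screened clients

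*Protocol article*

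**What the plan says.** All references are to the protocol article.

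- **Definition.** The Analysis section gives the outcome as "HPV positivity (number of HPV positive tests/number of screening tests". The denominator is every screening test, whatever the client's history.
- **Comparison.** The same section states "Primary and secondary outcomes will be calculated comparing data from the before (T0, > 24 months) and after (T1, 12 months) period". The Cervical screening data section likewise lists "HPV positive tests in the 2-years before and during the study period" as a secondary outcome.
- **Model.** The periods are compared descriptively and with "multi-level logistic regression models clustered on site and allowing for participants who are active in both periods". No term for screening history is named.
- **Subgroups.** The one stated subgroup analysis does not concern positivity: "A subgroup analysis will also be conducted of the primary outcome among women who have never screened or screened >10 years ago".
- **Who is to be tested.** Step 2 (Co-design) says "All strategies will aim to increase participation of under- and never-screened women and people with a cervix in cervical screening using HPV self-collection". The Sample size section puts the under-screened at about half or more of eligible clients and plans for their 12-month uptake to go from 20% to 40%.
- **Table 1.** Under Evaluation Framework, participation and under- or never-screened status are marked at both time points. Positivity appears only as "HPV positive tests #T1".

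**The concern.** The strategies work by changing who is tested. If they succeed, a larger part of the after-period denominator comes from under- and never-screened clients. If HPV positivity differs between them and up-to-date clients, the overall ratio moves even when nothing changes in either group. It stays free of this effect only if the two groups have equal positivity, for which the document gives no evidence, or if the mix of tests does not change, which is not what the strategies intend.

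At stake is the reading of one secondary outcome. A change in the crude ratio could not be attributed to a change within either group, and a flat ratio would not show that both groups were stable. The primary outcome, the recruitment target and the sample size are unaffected.

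**Working it through.** **The plan's own figures.** None is stated for HPV positivity. The sample size figures concern uptake, and they reproduce: 91 per arm for 20% versus 40% with a continuity correction, design effect 1 + 49 × 0.1 = 5.9, total 2 × 91 × 5.9 = 1073.8, that is 1074. They do not bear on this point beyond supplying the planned uptake.

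**Inputs**
- Under-screened proportion of eligible clients, u = 0.50 (Sample size section, which says about 50% or more).
- Uptake per 12 months in the under-screened, b = 0.20 before and 0.40 after (Sample size section).
- Testing rate per 12 months in up-to-date clients, r = 0.20. Assumed, range 0.10 to 0.30.
- Positivity in up-to-date clients, p_r = 8%, and in under-screened clients, p_u = 8, 10, 12 or 16%. Assumed, and held equal in both periods.

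**Formulas**
- Under-screened share of tests: s = u·b / (u·b + (1 − u)·r)
- Crude positivity: P = p_r + (p_u − p_r)·s
- Change in P = (p_u − p_r)·(s1 − s0) + within-group changes. The gap is taken at its before values, and the within-group changes are weighted by the after mix.

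**Share of tests**
- Before: 0.10 / (0.10 + 0.10) = 50%
- After: 0.20 / (0.20 + 0.10) = 67%
- Change: one sixth. The crude ratio therefore moves by about one sixth of whatever gap exists.
- With r = 0.10 the share goes from 67% to 80%. With r = 0.30 it goes from 40% to 57%.

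**Shift in crude positivity with no within-group change (r = 0.20)**

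| p_r | p_u | Before | After | Shift (points) | Odds ratio |
|---|---|---|---|---|---|
| 8% | 8% | 8.00% | 8.00% | 0 | 1.00 |
| 8% | 10% | 9.00% | 9.33% | +0.33 | 1.04 |
| 8% | 12% | 10.00% | 10.67% | +0.67 | 1.07 |
| 8% | 16% | 12.00% | 13.33% | +1.33 | 1.13 |

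For 8% versus 16%, the shift is +1.07 points at r = 0.10 and +1.37 at r = 0.30.

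**Opposite sign.** With p_r = 8% and p_u = 6%, the shift is (6 − 8) × 1/6 = −0.33 points.

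**Sensitivity to the baseline.** The Sample size section also mentions a lower uptake of 5-10%, before the policy change. Starting from 5% with r = 0.20, the share goes from 20% to 67% and the shift is 0 to +3.73 points over the same positivity range. The plan is built on 20%, so the smaller figures are the relevant ones.

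**The case against.** - **The before-after contrast is not settled.** If Table 1 governs, positivity is an after-period figure only and there is nothing to confound. This stands as a reason to reconcile the texts. It does not remove the point, because the Analysis and Cervical screening data sections both state the comparison.
- **The crude ratio is a legitimate yield measure.** Positives per test describes what testing returned. This stands. A reader might infer that the outcome cannot be interpreted at all, or that the investigators will present a rise as a change in disease or in test performance. The document supports neither: the aims concern participation, the success criterion does not use positivity, and no section reads a change in it causally.
- **Caution is already promised.** The plan says "Due to the small number of participating services, modelled findings and secondary subgroup analyses will be interpreted cautiously". The reason given is the number of services, not case mix, and the Limitations section deals with data quality and missingness. The caution helps but does not address this source of change.
- **Stratification may sit in an analysis plan that is not shown.** It may. The point therefore rests on what the article fixes (the ratio, the comparison and the model as described), and this limits it to an improvement.
- **The size has no anchor in the document.** Correct. A reader might infer a certain and sizeable rise. The range includes zero, and the sign depends on an unknown gap.
- **Prior status may not be readily available.** The primary outcome gives status at T0 and T1. The strata need status just before each test, and a client tested in the before period may already count as screened at T0. This stands and is a real cost.

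**Conclusion.** The point holds as a minor one about a stated secondary comparison. As written, the before-after change in HPV positivity mixes any within-group change with a case-mix term, and the strategies are designed to alter the mix behind that term. On the plan's 20% to 40% uptake, with half of clients under-screened and an assumed 20% routine testing rate, the case-mix term is about one sixth of the positivity gap: 0 to +1.33 points for 8% versus 8-16%, and negative if the gap runs the other way. The positivity values and the routine testing rate are assumptions, so neither size nor direction can be derived from the document. Whether the contrast exists at all depends on how Table 1 is reconciled with the text.

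**What to change.** 1. Keep the crude ratio and label it as descriptive yield.
2. In each period, also report positivity by screening status immediately before the test: up to date, under- or never-screened, and unknown.
3. Base any before-after statement or model on those strata, or on a model that includes that status.
4. Reconcile Table 1 with the Analysis and Cervical screening data sections on whether HPV positive tests are measured at T0 as well as T1.

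**Cost.** One further table and a few sentences, with no change to design, recruitment or the primary outcome. Strata will be small at some services, so intervals widen. Status before T0-period tests needs earlier screening dates, which may be incomplete given the record problems noted in the Introduction and Limitations; the unknown category makes that visible. Stratifying removes the effect of screening history only, so other differences in who is tested may remain within strata.

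### Before and after windows differ in length (more than 24 months against 12) with no adjustment, so test counts are not comparable and the planned 12-month contrast is not matched

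*Protocol article*

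**What the plan says.** The protocol article describes the comparison periods in four places.

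- **Analysis:** "Primary and secondary outcomes will be calculated comparing data from the before (T0, > 24 months) and after (T1, 12 months) period". The same section defines the primary outcome as the share of screen-eligible clients who are under- or never-screened at T1 compared with T0. Participation is a recorded screen in the previous five years over eligible clients. Self-collection and HPV positivity are shares of screening tests. The model is a multi-level logistic regression clustered on site; no offset or other term for period length is mentioned.
- **Cervical screening data:** the secondary outcomes, given as numbers as well as proportions, cover "HPV positive tests in the 2-years before and during the study period".
- **Sample size:** the effect is a movement from under-screened to screened, "from 20% in 12 months at baseline to 40%, with 80% power (2-alpha = 5%) and a conventional non-clustered design". The baseline figure is explicitly a yearly one: "to 20% per 12-month period".
- **Table 1 (Evaluation Framework):** participation and under- or never-screened status carry both T0 and T1, but the entry for collection method reads "Cervical screens by collection method (i.e., self- or clinician-collection) #T1", and HPV-positive tests are likewise listed at T1 only.

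**The concern.** The before window is at least twice as long as the after window and has no upper limit. Anything that accumulates with time has longer to accumulate before than after, which works against the intervention. The study is planned on a rate with the same 12-month base in both periods, so the stated windows do not deliver the planned contrast for that quantity.

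The open end also matters for calendar time. Self-collection was restricted until July 2022 (Introduction). A before window that runs back past that date includes months in which few clients could self-collect. That lowers the baseline self-collection share and works in favour of the intervention.

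Finally, a before-after comparison of collection method and HPV positivity needs a baseline value, and Table 1 does not schedule one. With three descriptions of the before window in play, an analyst could settle on one after seeing the data.

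**Working it through.** **Inputs.** From Sample size: 20% and 40% per 12 months, 80% power, two-sided 5%, 91 per arm unclustered, ICC 0.1, 50 clients per cluster per period, up to 12 clusters, 600 per period. From Analysis: before more than 24 months, after 12 months. From Setting: first implementation start 1 September 2024, last implementation end 8 September 2026.

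**1. Reproducing the plan's own figures.** The pooled two-proportion formula for 20% against 40% gives 82 per arm, and the continuity-corrected version gives 91, as stated ("would require 91 women and people with a cervix per arm"). The design effect is 1 + (50 − 1) × 0.1 = 5.9, and 2 × 91 × 5.9 = 1073.8, the stated 1074. With 600 per period the effective number is 600 / 5.9 = 101.7, and power for 20% against 40% over equal 12-month windows is about 88%.

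**2. Counts.** Take a closed group of 600 under-screened clients with a constant yearly rate of 20% before and 40% after.

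- Before, 24 months, compounded: 600 × (1 − 0.8²) = 600 × 0.36 = 216.
- Before, 24 months, linear: 600 × 0.20 × 2 = 240.
- After, 12 months: 600 × 0.40 = 240.

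A true doubling of the rate therefore appears as 216 to 240 screens against 240.

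**3. The powered transition, if cumulated over the stated windows.** The before proportion over m months is 1 − 0.8^(m/12) compounded, or 0.20 × m/12 linear. The after proportion is 40%.

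| Before window | Compounded | Linear |
|---|---|---|
| 12 months | 20% | 20% |
| 24 months | 36% | 40% |
| 30 months | 42.8% | 50% |
| 36 months | 48.8% | 60% |

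At 24 months the difference falls from 20 points to 4 or 0, and the risk ratio from 2.0 to 0.40 / 0.36 = 1.11 or 1.00. Power for 36% against 40% with 101.7 effective clients per period is about 8%; for 40% against 40% there is no effect to detect. Beyond 24 months the sign can reverse.

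**4. Outcomes whose formula contains no window length.** Under- or never-screened status is read at T0 and at T1. Participation looks back five years at both dates. The self-collection and HPV-positivity shares have tests as denominator, so numerator and denominator grow together. None of these is diluted by a longer before period.

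**5. Calendar reach.** Assume T0 coincides with the start of implementation. From July 2022 to 1 September 2024 is 26 months, so for the earliest site a before window longer than 26 months includes restricted-access time. The latest sites, with 12 months ending by 8 September 2026, start about September 2025 and have roughly 38 months after the policy change.

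**The case against.** The strongest reply is that the arithmetic in step 3 attaches to no outcome the article defines. The 12-month transition appears only under Sample size. The primary outcome is a status, participation has a fixed look-back, and the test-based outcomes are shares. On this reading the more-than-24-months phrase merely describes how far back records are drawn. This stands. A reader might infer from the windows sentence that the primary analysis has about 8% power, or that a true doubling would vanish from every outcome; the outcome formulas do not support that.

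A second reply is that contamination by pre-policy months is speculative, since two years before the earliest start is September 2022. This stands for a 24-month window and for later sites. It does not stand for a window with no upper limit at sites starting in late 2024.

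A third is that annualising counts is detail an article may leave to a fuller document. This carries less weight, because the article itself fixes the two windows, applies them to primary and secondary outcomes alike, and makes numbers part of the outcomes. Leaving a detail out differs from stating a rule that gives non-comparable figures.

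That the sample size rests on a transition rate while the primary outcome is a prevalence is a separate matter, which equal windows would not cure.

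**Conclusion.** The point holds in a limited form. The article states unequal windows, gives two descriptions of the before window (two years, and more than 24 months), plans on 12-month rates and states no adjustment for length. Followed as written, the counts of screens, self-collected screens and HPV-positive tests are not comparable: a true doubling shows as about 216 to 240 against 240. The change from 20% against 40% to 36% or 40% against 40%, with power of about 8% or less, applies only if the powered transition is cumulated over the stated periods. It assumes a closed group, a constant 20% yearly rate and a before window of exactly 24 months.

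The primary outcome, the five-year participation rate and the test-based proportions are not mechanically diluted. The self-collection share can still be biased in favour of the intervention at sites starting in late 2024 if the look-back passes July 2022. The documents do not show that it will, or by how much. The Table 1 mismatch is plain on the page.

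**What to change.** - State that T0 and T1 are status dates for the primary outcome, and that participation keeps its five-year look-back at each date.
- For transition rates, counts, collection method and HPV positivity, use equal windows: the 12 months ending at each service's T0 and the 12 months of implementation. Alternatively, express counts per eligible client per 12 months over a bounded look-back. Use no data before July 2022 in either case.
- Make the Cervical screening data and Analysis sections give the same window, and add T0 to the Table 1 entries for collection method and HPV-positive tests.

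The wording change is small. The cost is fewer before-period tests, so slightly less precise baseline shares, and a need for dated test extracts. Not every service may be able to supply these: the Introduction reports that local systems can prevent extraction of self-collection uptake at service level. Where that is so, the before value should be reported as unavailable rather than taken from a window of a different length.
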